## 10.6 Measures to Minimize Bias

### 10.6.1 Enrollment/ Randomization/ Masking Procedures

Participants will be randomly assigned to one of two equal-caloric diets for the entire study period: a low-fat diet (n=125) or a Mediterranean/low-carbohydrate diet (n=125). After 6 months of dietary intervention, each diet group will be further randomized into added PA groups (LF^PA+^, MED/LC^PA+^) or no added PA groups (LF^PA–^, MED/LC^PA–^) for the last 12 months of intervention. The randomization will be performed with an allocation ratio of 1:1 to the two treatment groups, within strata of baseline VAT area for the first randomization, and of address of residence (to ensure similar geographical distance from the gym) in the second randomization (in blocks of two). Participants will be randomized after all had been recruited, in one phase, after their strata characteristics will be defined.

The participants, who will be randomized in the same time point, will be aware of the intervention to which they will be assigned (open-label). Study investigators will be blinded to the intervention group identities.

### 10.6.2 Evaluation of Success of Blinding

Double Blind (Care Provider, Investigator, Outcomes Assessor)

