The second randomization will be performed after six months of the dietary intervention. The dietary groups will be further divided into PA (A+, B+) and non-PA (A-, B-) groups. The participants assigned to PA groups will get 12 months free supervise gym membership. The PA intervention will be mostly aerobic exercise training (80%) and resistance training three times a week, for 30 minutes in the first month, 50 minutes in the second to fifth months, and 80 minutes for months six to twelfth. The PA participants will be guided first in the gym with the support of the professional sport trainers. We will follow the PA participants online by electronic gym card recording their frequency of access and duration to the sport center and will call them frequently to encourage adherence.

***Intervention:*  Arm A:** the 2006 currently recommended diet by the American Heart Association (AHA) ^35^ (Low-fat) calorie restricted diet, a more revised statement since the AHA 2000; **Arm B:** guidelines^40^Low-carb/MED non-calorie restricted diet (n=125). Based on our preliminary results, low-carb and Mediterranean diets each showed beneficial effects on several biomarkers. Thus, here we suggest to utilize an optimized diet strategy which combines the beneficial components of low carb (low-carb) and Mediterranean (high monounsaturated) diets (**Table 2**). For both arms moderate physical activity will be equally introduced and monitored. The participants will be guided to exercise 150 min/week of moderate intensity, primarily in the form of initiating walking. This will be monitored by podometers that will be provided. The advantage of this strategy is that the podometer reflects both exercise thermogenesis (walking) as well as components of Non-exercise activity thermogensis (NEAT)^41^. The format and quality of the sessions will be kept constant to ensure equal treatment intensity, except for the specific instructions and paper material distributed for each diet strategy.

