*Strategies to promote and verify adherence^22^: i. Food color and nutrition data labeling:* Lunch is considered the main daily meal in Israel. As the self-serve cafeteria in the workplace is the exclusive source of lunch for the participants, we will label each food item and nutritional data for the entire cafeteria styles. After analyzing the recipes and raw foods using the Israeli nutritional database^42^, we will display in each food-label: calories, grams of carbohydrates, fat, and saturated fat per portion size. We will further color-code the food item labels by setting specific criteria to component contents of each diet. Each dish will be labeled with a full circle (= "feel free to consume") or half-circle (= "consume in moderation") according to the diet arm, using two different colors. *ii.* The entire intervention and most measurements will be performed in the workplace, continuously monitored by the nurse study. Furthermore, structured motivation telephone calls and ongoing messaging via the intranet communication system will be held by specifically-trained dietitians.

The participants will be required to fill in electronic questionnaires at baseline, 6, and 18 months, which include: i. a validated food frequency questionnaire (FFQ) ^43^ that includes 127 food items and 3 portion sizes pictures for 17-selected food items. The nutritional data will be analyzed in the Israeli nutrition database ^42^. ii. Physical activity questionnaire: transformation to metabolic equivalents ^39^. Medical information will be updated by the workplace medical center’s physicians. A uniquely-developed electronic interface for submitting the questionnaires will ensure the completeness of data by popping-up missing lines.^22^

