**Physical Activity Intervention**

Starting after the first 6 months of dietary intervention, participants who will be randomized to added PA will receive a free supervised gym membership for the following 12 months. The intervention will include monthly 60-minute educational workshops, and training group sessions at the gym, directed by a certified fitness instructor, who will be blinded to the assigned diets of the participants. The exercise program will include three sessions/week of mostly aerobic training. In the first month participants will start with low intensity of aerobic training at 65% maximum heart rate for 20 minutes and 10 minutes of resistance training. Exercise will gradually increase to 45 minutes of aerobic training at 80% of maximum heart rate and 15 minutes of resistance training. The resistance training will be increased from one set of weights with 60% of the maximum weight up to two sets with 80% of the maximum weight and will include: leg extension, leg curl, elbow flexion, triceps extension, lateral pull-down, lower back extension and bent leg sit-ups.

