## 10.3 Analysis Datasets

We will check the assumptions for all the statistical analyses to ensure that none were violated. We will perform intention-to-treat analyses, including all the participants, by imputing the missing observations for adipose tissues for the individuals with missing data at 18-months by the multiple imputation technique, with the following predictors: age, gender, baseline weight/ BMI and waist circumference at the end of the intervntion. For missing data of body weight, we will use the last observation carried forward.

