### 10.6.3 Breaking the Study Blind/Participant Code

The code will be blind until the end of the study.

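### Section 10.6.2 states care-provider blinding that the design does not have, and no blinding procedure is described for the waist and weight readings that enter the VAT analysis

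*Protocol*

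**What the plan says.** Three short sections of the Protocol describe masking. Section 10.6.1 says that participants "will be aware of the intervention to which they will be assigned (open-label", and then that "Study investigators will be blinded to the intervention group identities". Section 10.6.2, headed as an evaluation of blinding success, contains only the label "Double Blind (Care Provider, Investigator, Outcomes Assessor". Section 10.6.3 adds "The code will be blind until the end of the study".

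Other sections describe delivery and measurement:

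- **Diet (4.1, 6.1).** Clinical dietitians lead the sessions. Format and quality are held equal between arms "except for the specific instructions and paper material distributed for each diet strategy". A dietitian works with the kitchen to fit the food to each diet group. Motivational calls and intranet messages "will be held by specifically-trained dietitians".
- **Exercise (6.1, 4.1).** A certified instructor directs the gym sessions, "who will be blinded to the assigned diets of the participants". The study team follows exercise-arm participants through gym-card records and telephones them about adherence.
- **Access to investigators (7.9).** Participants may contact all investigators during the study.
- **Measurement (7.1.1).** MRI observers are blinded to group and time point. Waist is taken by hand with a tape and weight is recorded monthly; neither description mentions blinding.
- **Analysis (10.3, 10.4.1).** Missing 18-month adipose values are multiply imputed from age, gender, baseline weight/BMI and "waist circumference at the end of the intervntion". All models adjust for 18-month weight change.

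**The concern.** Blinding of care providers is a claim of protection against performance bias. If the people who teach, feed and encourage participants know the assignment, differences in effort or attention between arms can contribute to the outcome, and a reader must be able to allow for that. A report that repeats the Section 10.6.2 label would tell readers that this risk had been controlled.

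A second, smaller matter is assessment bias. The primary VAT reading has its own safeguard. The tape and scale readings have none described, yet both enter the VAT analysis: waist through imputation, and weight as a covariate. If the person holding the tape knows the arm, an arm-related error in waist could carry into the imputed part of the intention-to-treat VAT comparison.

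**Working it through.** **1. The label set against delivery, role by role.** This part needs no arithmetic.

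| Role | Claimed in 10.6.1–10.6.3 | What the other sections show |
|---|---|---|
| Participants | Open-label; not in the 10.6.2 list | Consistent |
| Dietitians | Blinded, as care providers | Give arm-specific instruction and material and fit food to diet group (4.1, 6.1): contradicted for diet |
| Fitness instructor | Blinded, as care provider | Blinded to diet; trains only those assigned to exercise (6.1): contradicted for exercise assignment |
| Investigators | Blinded, no list of persons | Team tracks and calls the exercise arm (4.1) and open-label participants can reach all investigators (7.9): doubtful, not refuted |
| MRI observers | Blinded, as assessors | Specific procedure in 7.1.1: supported |
| Waist and weight measurers | Blinded only through the general assessor label | No procedure described in 7.1.1: unsupported |

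**2. How waist reaches VAT.** Of the predictors in Section 10.3, age, gender and baseline weight/BMI are fixed at entry, and treatment arm is not listed. End-of-intervention waist is the only listed predictor carrying information from after randomisation. The route needs a participant with an 18-month waist and no usable 18-month MRI. It is zero where the MRI was read, and has no direct effect where the 18-month waist is missing too.

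**3. Size of the waist route.** The Protocol gives no missing-data rate, so every input below is an assumption.

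Shift in the VAT contrast = m × β × b, where

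- m = share with VAT imputed and waist measured, 5% to 15%;
- β = VAT change per cm of waist in the imputation model, 2 to 6 cm² per cm;
- b = between-arm error in waist, 0.5 to 2 cm.

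| Case | m × β × b | Shift (cm²) | Share of 3.57 cm² (Section 10.5) |
|---|---|---|---|
| Low | 0.05 × 2 × 0.5 | 0.05 | 1.4% |
| Mid | 0.10 × 4 × 1 | 0.4 | 11.2% |
| High | 0.15 × 6 × 2 | 1.8 | 50.4% |

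The range for m is borrowed from Section 2.1, where the earlier diet trial reports adherence of 95% at 1 year and 85% at 2 years. Applied to 250 participants it gives 0.05 × 250 = 12.5 to 0.15 × 250 = 37.5, or about 12 to 38 people. That is better read as an upper bound than as an estimate. It treats adherence in another trial as MRI completion here, and it assumes that everyone without an MRI still has a waist reading. Table 3 schedules both at month 18, so someone who has left would usually lack both.

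**4. Weight.** Because 18-month weight change adjusts all models, any arm-related error in weight would not be confined to participants with missing MRI. The documents offer nothing from which to size it.

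**The case against.** The strongest reply is that the primary endpoint is protected. VAT and hepatic fat are read by observers blinded to group and time point, waist is neither a primary nor a named secondary endpoint, and participant awareness is openly stated. The list in Section 10.6.2 omits participants, so it does not contradict Section 10.6.1 about them. All of this stands, and it keeps the waist route secondary.

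A reader might infer several stronger points that the documents do not support:

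- **That investigator blinding is impossible.** Open-label in Section 10.6.1 describes participants, and no section makes every investigator a deliverer of care. Sections 4.1 and 7.9 cast doubt on the blanket sentence without refuting it.
- **That trainers are simply unblinded.** Section 6.1 blinds the instructor to diet, and that safeguard should be kept.
- **That only the MRI readers could be blinded.** Besides the instructor's partial blinding, biochemistry is run at an outside laboratory (7.1.1) on samples marked only by serial number (13.4).
- **That waist is known to be measured unblinded.** The assessor label covers it on its face. What can be said is that no procedure is described, in contrast to MRI.
- **That the cafeteria labels or telephone calls reveal the arm to staff.** The labels mark dishes, and Section 4.1 does not say that the calls differ by arm. The case rests on the session content and the food adjustment.

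None of this rescues the care-provider claim. It concerns the rest of the label and the size of the consequence.

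**Conclusion.** The point holds for care providers. Section 10.6.2 asserts a blinding that the Protocol's own account of delivery contradicts: for dietitians as to diet, and for the fitness instructor as to exercise assignment. Calling the trial double-blind does not fit a study that is open to participants and to those who teach the diets. This conclusion rests on the text alone and needs no assumption.

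Investigator blinding is unsupported as written, because it names neither persons nor procedure. The same is true of waist and weight assessment.

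The consequence for VAT through waist is limited to participants with a waist reading but no MRI. On assumed inputs it runs from 0.05 to 1.8 cm², with a mid case of 0.4 cm², about 11% of the stated detectable difference. The high case needs all three assumptions at their extremes. It would go too far to conclude that the primary result is compromised. The correction should be made because it is cheap and because reports would otherwise claim a protection against performance bias that the trial lacks.

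**What to change.** Replace Section 10.6.2, and bring Sections 10.6.1 and 10.6.3 into line with it, using a statement such as:

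> Open-label to participants. Dietitians not blinded to diet. Fitness instructors blinded to diet but not to exercise assignment. MRI observers blinded to group and time point. Investigators blinded only where they deliver no intervention and do not track adherence.

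Drop the double-blind wording and the blanket care-provider claim from the Protocol and from all reports.

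Have existing clinic staff who are not told the arm take waist and weight, and say so in Section 7.1.1. If that cannot be arranged, label both as unblinded measures and add a sensitivity analysis that imputes VAT without end-of-intervention waist.

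The cost is a wording change, one staff instruction and possibly one extra analysis. The downside is that the stated level of blinding becomes less favourable.

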### 10.6.3 Breaking the Study Blind/Participant Code

The code will be blind until the end of the study.

# 11 SOURCE DOCUMENTS AND ACCESS TO SOURCE DATA/DOCUMENTS

All documents, include the singed inform consent will be hold in a lock room in the Radiolegy department in Soroka Medical Center.

# 12 QUALITY ASSURANCE AND QUALITY CONTROL

# 13 ETHICS/PROTECTION OF HUMAN SUBJECTS

## 13.1 Ethical Standard

The PI will ensure that this study is conducted in full conformity with the Declaration of Helsinki.

## 13.2 Institutional Review Board

The protocol, informed consent form, recruitment materials, and all participant materials were submitted and approved by the IRB (Medical Ethics Board and the Helsinki Committee of the Soroka University Medical Center, Israel). Any amendment to the protocol will be submitted for review and approval by the IRB before the changes are implemented to the study. All changes to the consent form will be IRB approved; a determination will be made regarding whether previously consented participants need to be re-consented.

## 13.3 Informed Consent Process

### 13.3.1 Consent/assent and Other Informational Documents Provided to Participants

Consent form describing in detail the intervention, study procedures, and risks are given to the
participant and written documentation of informed consent will be obtained prior to performing any study procedure.

### 13.3.2 Consent Procedures and Documentation

Informed consent is a process that will be initiated prior to the individual’s agreeing to participate in the
study and continues throughout the individual’s study participation. Extensive discussion of risks and
possible benefits of participation will be provided to the participants. Consent forms were IRB-approved and the participant will be asked to read and review the document. The investigator will explain the research study to the participant and answer any questions that may arise. All participants will receive a verbal explanation in terms suited to their comprehension of the purposes, procedures, and potential risks of the study and of their rights as research participants. Participants will have the opportunity to carefully review the written consent form and ask questions prior to signing. The participants will have the opportunity to discuss the study with their surrogates or think about it prior to agreeing to participate. The participant will sign the informed consent document prior to any procedures being done specifically for the study. The participants may withdraw consent at any time throughout the course of the trial. A copy of the informed consent document will be given to the participants for their records. The rights and welfare of the participants will be protected by emphasizing to them that the quality of their medical care will not be adversely affected if they decline to participate in this study.

## 13.4 Participant and data Confidentiality

To protect the participant confidentiality, immediately with the recruitment, each participant will be assigned a serial number. No personal identification will appear on any test or and sample, which will be marked only with a serial number. The list with participants' personal data and their serial number will be kept locked by the PI of the study. All the acquired data will be kept confidential and will be accessible only to the authorized staff.

Participant confidentiality is strictly held in trust by the participating investigators, their staff, and any additional research-involved personnel. This confidentiality is extended to cover testing of biological samples and genetic tests in addition to the clinical information relating to participants. Therefore, documentation, data, and all other information generated will be held in strict confidence. The study participant’s contact information will be securely stored at Soroka University Medical Center for internal use during the study. At the end of the study, all records will continue to be kept in a secure location for as long a period as dictated by local IRB and Institutional regulations.

Study participant research data, which is for purposes of statistical analysis and scientific reporting, will
be transmitted to and stored at the Ben-Gurion University of the Negev. This will not include the participant’s contact or identifying information. Rather, individual participants and their research data
will be identified by a unique study identification number. The study data entry and study management
systems used by clinical sites and by Ben-Gurion University of the Negev research staff will be
secured and password protected.

### 13.4.1 Research Use of Stored Human Samples,Specimens or Data

All the biological samples will be aliquoted and kept in the freezers of the nutrition center, which are accessible only to an authorized staff. At the end of the study, according to the participants’ consent, the samples collected under this protocol will be kept for future studies, for which we will separately submit the required documents and additional informed consent forms to IRB to obtain the proper approval (e.g. genetic sub-study). Data will be kept in password-protected computers. Only investigators will have access to the samples and data.

## 13.5 Future Use of Stored Specimens

With the participant’s approval and as was approved by local IR, coded biological samples will be
stored at the nutrition center of BGU. These samples could be used for further research.

After the study is completed, coded, archived data will be transmitted to and stored at the
BGU Data Repository, under the supervision of [name], for use by other researchers including those outside of the study. For any future studies, a separate request for the study approval will be submitted to the Medical Ethics Board and the Helsinki Committee of the Soroka University Medical Center (IRB). To protect the participants’ confidentiality, all the stored specimens and/or data will be coded. Future studies may include performing genetic testing.

During the conduct of the study, an individual participant can choose to withdraw consent to have
biological specimens stored for future research.

# 14 DATA HANDLING AND RECORD KEEPING

## 14.1 Data Collection and Management Responsibilities

Data collection is the responsibility of the clinical trial staff at the site under the supervision of the site
PI. The investigator is responsible for ensuring the accuracy, completeness, legibility, and timeliness of
the data reported.
All source documents should be completed in a neat, legible manner to ensure accurate interpretation
of data. When making changes or corrections, cross out the original entry with a single line, and initial and date the change. DO NOT ERASE, OVERWRITE, OR USE CORRECTION FLUID OR TAPE ON THE ORIGINAL.

Copies of the electronic CRF (eCRF) will be provided for use as source documents and maintained for
recording data for each participant enrolled in the study. Data reported in the eCRF derived from source
documents should be consistent with the source documents or the discrepancies should be explained
and captured in a progress note and maintained in the participant’s official electronic study record.
Clinical data (including AEs, concomitant medications, and expected adverse reactions data) and clinical
laboratory data will be entered into the designated data storage system, which will include password protection and internal quality checks, such as automatic range checks, to identify data that appear inconsistent, incomplete, or inaccurate. Clinical data will be entered directly from the source documents.

## 14.2 Study Records Retention

Study documents will be retaine for 2 years after the final research report submission.

## 14.3 Protocol Deviations

A protocol deviation is any noncompliance with the clinical trial protocol, GCP, or MOP requirements.
The noncompliance may be either on the part of the participant, the investigator, or the study site staff.
As a result of deviations, corrective actions are to be developed by the site and implemented promptly.

The PI and the study staff is responsible for knowing and adhering to the IRB requirements.

